### Sample size

In calculating the sample size, we assumed a power of 90% and α value of 5%, in order to detect a difference of 1.6 days with migraine with a standard deviation of 2.8 days; this implies a sample size of 72 per group in a design with three equal groups. We propose to recruit 270 patients in order to allow for a 20% withdrawal rate.

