#### Statistical analysis

Two types of population will be analysed: (1) population per intention to treat (ITT), with all the patients randomised; (2) population per protocol (PP), including only the patients presenting minor differences from the protocol. During analysis, the study groups will be anonymised in order to minimize biased reporting.

The baseline variables among the different groups will be compared to test the homogeneity produced by random allocation, in terms of the differences of means and proportions. The magnitude of the difference in the possible unbalancing produced by the random allocation among the groups will be evaluated using ratios of means and proportions (using that of the sham group as the reference level), and the final fit will be calculated by secondary analyses with multiple linear regression models. In the raw analysis (without fitting), significance tests will be used for the comparisons between *k *samples (parametric or not, depending on whether the distribution of the results variables is asymmetric or otherwise, and on the homogeneity of their variances), taking the control group (group C) as the reference level, and using comparison tests for the differences of the means in the main results variable (DWM1), both for the intergroup comparisons (for independent samples) and for the comparisons between the baseline and the final levels for each group (in the latter case, using tests for non-independent or paired samples).

For the main results variable (DWM1), linear regression models will be constructed, adjusted for the baseline level and analysing per ITT. The group variables will be included, taking the control group as a reference, together with the sociodemographic variables (age and sex) and the baseline variables of the severity of the complaint (pain intensity and frequency). We will adjust for possible confounders using criteria of statistical significance and of confusion. The detection of possible interactions with the treatment group variable will be evaluated by criteria of statistical significance for the corresponding interaction terms. The level of significance will be established at α < 0.05. The model will be reconstructed, removing all the observations with Cook's distances above the 90^th ^percentile of the distribution, in order to test the consistency of the results obtained.

It is our intention to perform an economic analysis from the standpoint of the Andalusia Public Health Service.

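### The consistency refit removes the 10% of patients with the largest Cook's distances whatever their size, so its confidence intervals are too narrow and its type I error is about 14%; the primary regression is unaffected

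*Protocol article*

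**What the plan says.** The Statistical analysis section of the protocol article makes a regression the main model for DWM1, the change in days with migraine from baseline to weeks 9–12: "linear regression models will be constructed, adjusted for the baseline level and analysing per ITT". The model holds two group indicators with the control group as reference, age, sex, and baseline pain intensity and frequency. The significance level follows: "The level of significance will be established at α < 0.05". The next sentence is the consistency step: "The model will be reconstructed, removing all the observations with Cook's distances above the 90^th ^percentile of the distribution", and its purpose is given as "in order to test the consistency of the results obtained".

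The section sets no absolute size of Cook's distance for deletion, no correction of the standard errors afterwards, and no criterion for calling the two fits consistent.

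**The concern.** The cut-off is a rank, not a size. Every dataset has a top tenth of Cook's distances, so the rule deletes patients even when none has unusual influence. Those deleted are mainly patients with large residuals. The refit then estimates the residual variance from data whose extremes were cut off, as if no selection had taken place, and its standard errors come out too small.

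At stake is what the check can show. A refit that reports a narrower interval and a smaller p-value from fewer patients looks like support for the primary result, although the gain follows partly from the deletion rule.

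**Working it through.** **Inputs from the protocol article.** Sample size section: difference 1.6 days, SD 2.8 days, 72 per group (216), recruitment of 270 (90 per group). Statistical analysis section: the covariates, the 0.05 level and the deletion rule. **Assumptions:** two-sided tests, and the error distribution, since neither is stated. Normal errors are the base case; t with 5 and 3 degrees of freedom and a skewed gamma give a range.

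**The plan's own figure.** The plan says "this implies a sample size of 72 per group in a design with three equal groups". The usual two-group formula gives 2 × (1.960 + 1.282)² × 2.8² / 1.6² = 64.4, so 65 per group (66 by the t test). The 72 is thus not reproduced, but 216 / 0.8 = 270 is. This has no bearing on the present point, because the results are nearly the same at 72 and 90 per group.

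**Number deleted.** 22 / 216 = 10.2%; 27 / 270 = 10.0%. Cook's distance is D = e² h / [p s² (1 − h)²], with residual e, leverage h, p coefficients (here 8) and residual variance s². In 8,000 simulated null trials at 72 per group the average 90th percentile of D was 0.013. That lies below even the lenient 4/n = 4 / 216 = 0.019, so patients of unremarkable influence are deleted.

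**Simulation.** Each trial was fitted by least squares with two group indicators, baseline, age, sex, intensity and frequency. Patients above the 90th percentile of D were removed, the model was refitted, and the ordinary t test and 95% interval for one contrast with control were recorded. There was no true effect, and each row rests on 10,000 trials. The Monte Carlo error at 14.4% is √(0.144 × 0.856 / 10,000) = 0.35 percentage points.

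| Errors | Per group | Covariates | Reported SE, refit / full | True SD of estimate in days, full → refit | Coverage, refit | Type I error, full → refit |
|---|---|---|---|---|---|---|
| Normal | 72 | yes | 0.848 | 0.469 → 0.536 | 85.4% | 4.8% → 14.4% |
| Normal | 72 | no | 0.831 | 0.463 → 0.532 | 84.6% | 4.8% → 15.2% |
| Normal | 90 | yes | 0.849 | 0.417 → 0.476 | 85.6% | 4.7% → 14.2% |
| Normal | 90 | no | 0.832 | 0.416 → 0.480 | 84.4% | 5.0% → 15.4% |
| t, 5 df | 72 | yes | 0.753 | 0.470 → 0.455 | 87.2% | 4.9% → 12.5% |
| t, 3 df | 72 | yes | 0.651 | 0.470 → 0.365 | 88.3% | 4.8% → 11.4% |
| Gamma | 72 | yes | 0.738 | 0.475 → 0.450 | 86.8% | 5.3% → 13.0% |

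Repeat runs of the first row gave 13.9% to 14.4%.

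**Check by hand, first row.** The full-model SD should be about 2.8 × √(2/72) = 0.467, which agrees. The refit reports about 0.848 × 0.469 = 0.398 against a true SD of 0.536, a ratio of 0.742. A nominal 1.96 is then really 1.96 × 0.742 = 1.454, whose two-sided normal tail is 14.6%. The true SD rises by 0.536 / 0.469 − 1 = 14%. With heavy-tailed or skewed errors the true SD falls, but the reported standard error falls further, so the intervals are still too narrow.

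**How often conclusions change.** With normal errors and no effect, about 10% of non-significant contrasts became significant in the refit, and about 86% of false-positive primary results stayed significant. These agree with the total: 0.95 × 0.10 + 0.05 × 0.86 = 13.8%. The chance that at least one of the two contrasts with control is falsely significant goes from 8.7% in the full model to 24.5% in the refit.

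**Other cut-offs.** Deleting at D > 4/n removes about 11 of 216 patients and gives 11.1%. Deleting at D > 1 removed nobody in 3,000 trials and left the test unchanged (5.5% before and after).

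**The case against.** The refit is a secondary check. The plan does not let it replace the primary result or declare efficacy, and it does not say that consistency will be judged by p-values or intervals. If only coefficients are compared, the check is noisy but not misleading: mean refit estimates were 0.00, 0.80 and 1.61 days for true effects of 0, 0.8 and 1.6. At the planned 1.6 days, full model and refit reject almost equally often (91.8% and 93.4%). All of this stands, and it limits the reach of the point.

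It does not remove the point. The 0.05 level is set in the sentence just before the refit, so a reader will naturally look at the refit's p-values and intervals, and those are wrong.

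Three stronger readings are tempting, and the documents do not support them:

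- That the trial's type I error is 14%. The primary regression keeps all patients and stays near 5%.
- That the refit generally turns null results into significant ones. About nine in ten non-significant contrasts stay non-significant, and about 14% of false-positive primary results lose significance.
- That the refit contradicts the intention-to-treat principle. The plan ties that population to the main model, and an influence check by deletion departs from it by design.

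**Conclusion.** The deletion rule is badly fixed as written, but the fault is confined to the consistency refit. With normal errors its reported standard error is about 15% too small relative to the full model while the estimate is about 14% more variable. Coverage is about 86% and type I error about 14%, with a range of about 11% to 15% over the error shapes and models tried. These figures rest on assumed error distributions, two-sided tests and ordinary least-squares inference after deletion.

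The primary estimate, its error rate and the sample size are untouched. Since most false-positive primary results would survive the refit, its p-values and intervals cannot be offered as evidence that the primary result is robust. The change should be made, but the primary analysis does not depend on it.

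**What to change.** Replace the percentile deletion with a robust regression, for example a Huber or MM-estimator, on all intention-to-treat patients, for the same contrasts and covariates as the primary model. Name the estimator and its tuning constant in advance. The MM-estimator also limits the effect of high-leverage patients. The error rate of these estimators was not simulated here; the reason for the choice is that they downweight extreme patients and use standard errors designed for that weighting.

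Alongside it, list patients with high Cook's distance and give the leave-one-out range of each group effect, as description only. Report no p-values or confidence intervals from a reduced set.

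Two substitutes would not do. HC3 or bootstrap standard errors alone leave the least-squares estimate unchanged, so they do not examine influence. Refitting after a 4/n cut-off still gives about 11% type I error, so 4/n is usable only for the listing.

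The cost is a change of wording and some analysis code. Data collection, sample size and trial conduct are not affected.
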